*Setting and site selection*: We recruited sites (Fig. 2 below) from the Women’s Health Practice-Based Research Network (PBRN), a network that provides a research infrastructure for investigators seeking to increase inclusion of women in VHA research or conduct multi-site women’s focused research in VHA. Comprised of approximately 70 VA sites that see one-half of women Veteran VA users, the PBRN helps investigators overcome the challenges of multi-site studies through the engagement of Site Leads with established working relationships with local clinicians and facility leadership. Sites were also recruited in collaboration with regional leadership in four regional Veterans Integrated Service Networks (VISNs). Each VISN was selected based on leadership’s interest in the EBPs, priorities for women Veterans’ preventive health, and our history of collaboration.

*Low-performing sites*: Our team has a long history of working with sites to improve women Veterans’ health, including QI efforts in low-performing sites. For the current project, a number of our sites are designated low-performing sites based on site visit assessment data.

*Patient eligibility and selection*: Women Veteran VA users are eligible for each EBP as follows: (1) *Virtual DPP*—overweight/obese women Veterans (BMI≥25 kg/m^2^ [≥23 if Asian]) with history of prediabetes (defined as either an HbA1c 5.7-6.5% or fasting blood glucose 100–125 mg/dL or oral glucose tolerance test 140–199 mg/dL) or history of gestational diabetes (GDM) or high risk on diabetes screening questionnaire. Women will receive invitation letters or be referred to the program by a healthcare provider and self-register with a CDC-recognized virtual DPP provider. (2) *TLC*—all women Veterans (who are not pregnant) are eligible to participate in TLC. Women will be referred to the program by a healthcare provider and will receive an outreach call from contracted health coaches to enroll. (3) *ROSE*—All pregnant women Veterans are eligible. Women will be identified and recruited by the site pregnancy/maternity care coordinator or other women’s health staff. As part of each implementation strategy (REP and EBQI, see below), sites will determine their own locally relevant recruitment strategies to engage 40 women Veterans/site in virtual DPP or TLC, and all interested pregnant women in ROSE.

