##### Cluster-randomized trial of the implementation strategies

*Randomization*: For this cluster-randomized trial, we will randomize sites clustered within four VISNs to either REP or EBQI (Fig. 2). Two VISNs will implement virtual DPP and two VISNs will implement TLC. To ensure adequate number of pregnant women for ROSE, all four VISNs will have the option to implement ROSE for their pregnant patients. With our focus on increasing access to preventive services for women living in rural areas, sites that serve rural Veterans will be selectively recruited. Rural sites tend to be community-based outpatient clinics (CBOCs) as opposed to large VA medical centers (VAMCs), so at least one additional CBOC in each VISN will invited to participate. Because the same leadership team may oversee VAMC and CBOC operations, any VAMC and CBOC that share a leadership team will be randomized as a unit to avoid contamination across implementation strategies. Therefore, a total of 20 individual VA sites (VAMCs or CBOCs) will be included from four VISNs. With the balanced design, half of the sites (*N*=10) will receive REP and half will receive EBQI (*N*=10).

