
**Table ﻿2 Tab2:** Measures for Aim 2a

EBP	Primary outcome	Participation and engagement	Primary impact performance goals	Clinical outcomes and other VA performance measures
Virtual DPP	• # of eligible patients who register at the DPP site (i.e., enroll) • # of eligible patients who participate in virtual DPP and attend at least one session	• Average # of DPP sessions attended^a^ • Proportion who completed ≥3, ≥9 and ≥16 DPP sessions^a^ • Change in reported physical activity^a^ • % weight change at 12 and 24 months	Increase participation in weight management program (e.g., MOVE)	• Overweight/obesity/weight management • Prevalence of prediabetes, diabetes, and incident type 2 diabetes • HEDIS: Hypertension and Diabetes
TLC	• # of provider referrals for TLC • # of patients w/ TLC encounter (enrolled)	• Average # of TLC sessions completed^a^ • % with SMART goal^a^ • % with behavioral change (physical activity; diet: fruit, vegetable, and sugary beverage intake; stress and coping; and weight)^a^	Increase in telehealth encounters for prevention (e.g., Whole Health)	• Overweight/obesity/weight management • Prevalence of prediabetes, diabetes, and incident type 2 diabetes • HEDIS: Hypertension and Diabetes
ROSE [4]	• # of provider referrals for ROSE • # of patients w/ ROSE encounter (enrolled)	• Average # of ROSE sessions completed^a^ • Depression screening	Increase in telehealth care for mental health	• # of patients that return to VA post-partum (utilization of VA health services in the 12 months post-partum) • Mental health/depression

^a^This data will be collected as part of the EBP. All other data will come from CDW

We will include data on-site-, provider-, and patient-level variables from VA administrative data or our operations partners. For the sites, we will include facility type (VAMC or CBOC) and size, women panel size, proportion of women at site, type of comprehensive primary care model for women Veterans [4], number of designated women’s health providers, and urban/rurality. Provider characteristics will include provider type (MD or NP) and whether the provider is a designated women’s health provider. Patient-level controls will include sociodemographic characteristics, comorbidity including diabetes and cardiovascular risk, service-connected disability status, utilization, and the most common ICD-10 codes related to pregnancy status.

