*Data analysis plan for Aim 2a*: We will use generalized linear models to evaluate the effectiveness of the intervention strategies for implementation of the EBPs in increasing women’s participation in telehealth-based preventive care. The models will account for clustering at the site level as well as incorporating site- and patient-level covariates outlined above. The main outcomes will include the composite measures of the proportion of women referred and enrolled in preventive telehealth care services, and the primary independent variable of interest is implementation using REP versus EBQI. We will conduct subgroup analyses by EBP to examine if the effects of the implementation strategies on proportion referred and enrolled vary by EBP (TLC or virtual DPP) as well as evaluate the effect on the *primary impact performance metrics* for telehealth care (weight management programs, Whole Health, and telemental health). In each model, we will examine the potential moderating effects of site-level characteristics (e.g., facility type, size, women’s health care program model, etc.). Adjustment for clustering will be performed using Stata v15, and we will evaluate goodness-of-fit using Mallows statistic (Cp). For DPP and TLC, we will use appropriate generalized linear models to assess weight and behavior change and examine differences by levels of participation (number of sessions completed). For ROSE, we will assess depression scores by levels of participation.

*Power calculations*: We based power calculations on the study’s basic single level of clustering sample design, where sites are randomized to receive either REP or EBQI to implement the EBPs. To detect a moderate effect size in terms of Cohen’s *D* (.26 standard deviations) between REP and EBQI, with 20 sites, and cluster adjustment (ICC=.01) with 80% power we will recruit 40 women per site (total of 800 women). We have considered all 20 sites to be separate clusters in terms of these calculations.

Aims 2b–2d are summarized in Table 3.

**Table 3 Tab3:** Overview of Aims 2b–2d

Method	Timing (per QUERI Roadmap)			Intended analyses
	Pre-implementation	Implementation	Sustainment	
Site tracking log	• Meeting minutes • Templated reflections • Stages of Implementation Completion (SIC)			2b: SIC 2c: Adaptations, experiences of EBP implementation 2d: cost

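### VISN decides whether a site runs virtual DPP or TLC but is absent from the stated primary model, and the planned DPP-versus-TLC comparison of strategy effects cannot be separated from VISN

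*Protocol article*

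**What the plan says.** The paragraph on randomisation (Protocol article, Cluster-randomized trial of the implementation strategies) states that "we will randomize sites clustered within four VISNs to either REP or EBQI". It then fixes the EBP by VISN: "Two VISNs will implement virtual DPP and two VISNs will implement TLC". ROSE is handled differently: "all four VISNs will have the option to implement ROSE for their pregnant patients". The paragraph on setting and site selection adds that "Each VISN was selected based on leadership’s interest in the EBPs"; the article describes no random assignment of EBP to VISN.

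The data analysis plan for Aim 2a says: "The models will account for clustering at the site level as well as incorporating site- and patient-level covariates outlined above". The site-level list below Table 2 begins "we will include facility type (VAMC or CBOC) and size, women panel size, proportion of women at site" and goes on to the women's primary care model, the number of designated women's health providers and rurality. Provider and patient factors follow. Neither VISN nor EBP is listed. The main predictor is REP versus EBQI. Subgroup analyses are then planned "to examine if the effects of the implementation strategies on proportion referred and enrolled vary by EBP (TLC or virtual DPP"). The power paragraph uses one level of clustering, with all 20 sites as separate clusters.

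The section on EBQI says that the findings will guide which strategy to pair with which EBP in which setting.

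**The concern.** There are two separate problems.

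**Primary contrast.** The outcome is a proportion of eligible women, and eligibility differs sharply by EBP. TLC is open to every woman Veteran who is not pregnant. DPP requires overweight or obesity plus prediabetes, a history of gestational diabetes, or a high screening score. The routes of entry differ too: self-registration for DPP, provider referral and an outreach call for TLC. Baseline proportions will probably differ between the two pairs of VISNs. Without a VISN or EBP term, that difference becomes unexplained between-site variation.

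**EBP comparison.** Asking whether REP versus EBQI works differently for DPP and for TLC means comparing two VISNs with two others that were chosen on leadership interest. A difference could reflect leadership, region or EBP, and the design cannot tell which. If it were read as evidence for matching a strategy to an EBP, policy could rest on a contrast between VISNs.

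**Working it through.** **The plan's own figure.** Inputs from the power paragraph: d = 0.26, 20 sites, 40 women per site, ICC 0.01, 80% power. Alpha is not stated; two-sided 0.05 is assumed.
- Design effect = 1 + 39 × 0.01 = 1.39.
- 233 per arm × 1.39 = 324 per arm, 648 in total, against the stated 800.
- At 800, power is 87.7% (normal) or 83.9% (t, 18 df).

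The stated size errs on the safe side, and the mismatch does not bear on this point. The figure of about 84% is the baseline for step 3.

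**1. Aliasing (no assumed rates).** Design matrix for 20 sites, with five per VISN for illustration:
- VISN + arm: rank 5. Adding EBP: still 5, so a VISN term absorbs DPP versus TLC.
- VISN + VISN × arm: rank 8. Adding EBP × arm: still 8.
- VISN + arm + EBP × arm: rank 6. The interaction can be computed if VISN × arm is left out, but it is then an EBP effect only if the strategy effect is the same in both VISNs sharing an EBP.

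**2. Precision lost by pooling.** Assumed: enrolment rates, ICC 0.02 within EBP, equal numbers of DPP and TLC sites. With P the mean of p(1−p) over the two EBPs:
- site variance within EBP = 0.02 × P
- between-EBP variance B = ((p_DPP − p_TLC)/2)²
- sampling variance of a site mean at 40 women = 0.98 × P/40
- SE ratio = √((W + B)/W), where W is site variance alone (very large sites) or site plus sampling variance (40 women)

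| DPP/TLC | P | Site variance | B | Sampling | Ratio, 40 women | Ratio, very large sites |
|---|---|---|---|---|---|---|
| 10%/2% | 0.0548 | 0.001096 | 0.001600 | 0.001343 | 1.29 | 1.57 |
| 8%/3% | 0.05135 | 0.001027 | 0.000625 | 0.001258 | 1.13 | 1.27 |
| 6%/4% | 0.0474 | 0.000948 | 0.000100 | 0.001161 | 1.02 | 1.05 |

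For 10%/2% at 40 women: √((0.001096 + 0.001343 + 0.001600)/(0.001096 + 0.001343)) = √(0.004039/0.002439) = 1.29.

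**3. Power by simulation.** d = 0.26, site ICC 0.01, 40 women per site, five sites per VISN assumed, 6,000 runs per setting, allocation balanced as nearly as possible within VISN:

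| Assumed VISN ICC | Power, VISN omitted | Power, VISN fixed | Type I error, VISN omitted |
|---|---|---|---|
| 0 | 84% | 82% | 5.0% |
| 0.01 | 78% | 82% | 3.9% |
| 0.02 | 72% | 82% | 3.0% |
| 0.05 | 54% | 82% | 1.7% |

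If allocation is not balanced within VISN, type I error without VISN stays near 5%. Power with VISN omitted is 85%, 76%, 69% and 57%; with VISN fixed it is 77%, 77%, 75% and 77%.

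**4. Chance imbalance.** With 6:4 DPP sites and 4:6 TLC sites (REP:EBQI) at 10%/2%, the arm means with no strategy effect are 0.6 × 10 + 0.4 × 2 = 6.8% and 0.4 × 10 + 0.6 × 2 = 5.2%, a spurious 1.6 points in that allocation. With 5:5 in each EBP the shift is zero.

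**5. Strategy-by-EBP test.**
- SE within one EBP (200 women per arm) = √(2 × 1.39/200) = 0.118 SD.
- SE of the difference between EBPs = 0.118 × √2 = 0.167 SD.
- Detectable difference at 80% power: 0.50 SD with sites as units (16 df); 0.94 SD with VISNs as units (2 df, no added VISN variance).
- If EBP is irrelevant but the strategy effect varies across VISNs with an assumed SD of 0.05, 0.10 or 0.20, the variance becomes 0.0278 + SD². A site-only test then rejects 6%, 9% or 21% of the time.

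**The case against.** The case on the other side has real force.

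- **Bias.** A reader might infer that omitting VISN biases REP versus EBQI. The documents do not support that: sites are randomised, so the contrast is unbiased over allocations. The 1.6 points belong to one hypothetical allocation. If allocation is balanced within VISN, the test without VISN is conservative.
- **Unknown layout.** Sites per VISN are not given, stratification by VISN is not stated outright, and Fig. 2 is not shown. An even split by EBP may have been arranged: 3:2 in one VISN and 2:3 in the other VISN with the same EBP gives 5:5. This stands, so imbalance is a risk and not a fact.
- **Scope.** A reader might infer that VISN fixes every EBP, or that the EBP results are worthless. Neither follows. ROSE is open to all four VISNs, and REP versus EBQI within DPP sites, or within TLC sites, remains randomised. The planned question concerns strategy effects by EBP, not an EBP main effect.
- **Detail for an analysis plan.** A stratum term is often left to the SAP, and separate analyses by EBP would remove the scale problem. This stands only in part: the article does state the clustering level, the covariates and a pooled main contrast with EBP as a subgroup question, and that specification does not fit its own allocation structure.
- **Degrees of freedom.** Twenty clusters less intercept and arm leave 18. At least seven site covariates reduce that to about 11, and VISN to about 8, or fewer if units with shared leadership are counted as single clusters. This stands and shapes the remedy.

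**Conclusion.** The point holds in two parts of different strength.

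The aliasing is certain. DPP versus TLC is a contrast between two pairs of VISNs, so a difference in strategy effect between them cannot be told apart from VISN-by-strategy variation. On its own it cannot support pairing strategies with EBPs.

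The primary-model part is a matter of precision. The standard error is inflated about 1.02 to 1.29 times at 40 women per site, and up to 1.57 times with very large sites. These figures rest on assumed enrolment rates and an assumed ICC of 0.02, because the article gives no rates. The effect could be trivial if DPP and TLC uptake turn out alike.

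**What to change.** 1. Add VISN as a fixed effect to the primary REP-versus-EBQI model. It takes 3 df and absorbs DPP versus TLC.
2. Shorten the list of site-level covariates if needed, since only 20 clusters are available.
3. State whether allocation was balanced within VISN, and how many sites each VISN contributes.
4. Report REP versus EBQI separately within DPP and within TLC, with intervals, as randomised estimates. Each will be imprecise: power for 0.26 SD within one EBP is about 49% (t, 8 df).
5. State that any DPP-versus-TLC difference in strategy effect is descriptive and confounded with VISN, and qualify the aim of matching strategies to EBPs accordingly. A VISN term does not cure this part.

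The cost is wording and a few cluster-level degrees of freedom. If VISN variance is zero, the term costs about 2 points of power with allocation balanced within VISN (84% to 82%), and about 8 points without such balance (85% to 77%). No site, patient or data collection changes.

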**Fig. 2 Fig2:**
[figure not shown]
Site-level randomization

*Aim 2a: Data sources*—We will use VA administrative data in the Corporate Data Warehouse (CDW) via the VA Informatics and Computing Infrastructure (VINCI) platform to examine EBP access and engagement and will monitor changes and trends in VA performance measures using the Reporting, Analytics, Performance, Improvement & Deployment’s Electronic Quality Measurement (eQM) portal. Since many of the interactive algorithms available on the eQM portal are not available by site and by gender, we will use the algorithms and data available on the portal and merge patient-level data in CDW to create gender-specific performance measures focusing on diabetes, hypertension, and depression/mental health. Additional engagement and outcome data will also be collected from each EBP delivery including number of sessions/modules completed, and program-specific measures.

*Aim 2a: Measures*—These fall into four basic categories shown in Table 2. The *primary outcomes of interest* are access to and engagement in telehealth care for preventive services, measured by referrals and enrollment. We will create composite measures of the proportion of women who participate in preventive telehealth care services for each EBP (# participate/# eligible). The primary outcomes for virtual DPP include the number of women who self-register for DPP (i.e., enroll) and the number who participate in virtual DPP (i.e., complete at least one online DPP module). For TLC and ROSE, the primary outcomes include the number of provider referrals for the programs and number of women Veterans with enrollment encounters. Parallel encounter coding will be developed for ROSE with the guidance of our Office of Primary Care. *Participation and engagement* outcomes collected by EBP are based on the average number of sessions completed and behavior changes documented during the program (e.g., weight change, increase physical activity, depression screens). For virtual DPP, we will assess rates of participation and engagement according to CDC standards for DPP delivery (i.e., average number of sessions attended, proportion who completed ≥9 and ≥16 sessions, etc.). For TLC, rates of participation and engagement are at ≥3 calls and ≥8 calls based on guidance provided by VA national offices regarding meaningful levels of contact with this EBP. For ROSE, maternity care coordinators (or comparable role) and ROSE facilitators will collect data on the number of sessions completed and proportion of completion of postnatal depression screens among participants. The *primary impact performance goals* for the EBPs will be based on performance metrics for telehealth care. For virtual DPP, we will monitor site-level performance measures for participation in weight management programs (e.g., MOVE!). For TLC, we will monitor site-level changes in telehealth encounters for prevention (e.g., Whole Health). For ROSE, we will monitor site-level changes in the use of telemental health and site-level changes in number of prenatal referrals sent out of the VA. Across all EBPs, we will also monitor metrics for use of telehealth services by women Veterans living in rural areas. Secondary outcomes of interest will include *clinical outcomes and other VA performance measures* related to each EBP. For virtual DPP and TLC, we will examine trends in clinical outcomes including percent weight change over 12 and 24 months, prevalence of hypertension, pre-diabetes, and diabetes. We will also examine trends in incident type 2 diabetes (≥1 inpatient diagnosis or any combination of ≥2 within 24 months: A1C≥6.5%, or fasting glucose≥126, or random glucose ≥ 200 or 2-h 75-g oral glucose tolerance test ≥ 200, or outpatient diagnosis code, or anti-hyperglycemic medication claim except metformin) [38, 39]. The VA (HEDIS) performance measures for diabetes and hypertension focus on proportion with guideline-recommended level of control among patients with the condition. Although our project is focused on prevention, we will track these measures because EBPs focused on lifestyle behavior change could impact level of control among diabetics and patients with hypertension. For ROSE, we will examine trends in postpartum attrition from VA among pregnant women through utilization of VA health services in the 12 months post-partum.

**Table ﻿2 Tab2:** Measures for Aim 2a

EBP	Primary outcome	Participation and engagement	Primary impact performance goals	Clinical outcomes and other VA performance measures
Virtual DPP	• # of eligible patients who register at the DPP site (i.e., enroll) • # of eligible patients who participate in virtual DPP and attend at least one session	• Average # of DPP sessions attended^a^ • Proportion who completed ≥3, ≥9 and ≥16 DPP sessions^a^ • Change in reported physical activity^a^ • % weight change at 12 and 24 months	Increase participation in weight management program (e.g., MOVE)	• Overweight/obesity/weight management • Prevalence of prediabetes, diabetes, and incident type 2 diabetes • HEDIS: Hypertension and Diabetes
TLC	• # of provider referrals for TLC • # of patients w/ TLC encounter (enrolled)	• Average # of TLC sessions completed^a^ • % with SMART goal^a^ • % with behavioral change (physical activity; diet: fruit, vegetable, and sugary beverage intake; stress and coping; and weight)^a^	Increase in telehealth encounters for prevention (e.g., Whole Health)	• Overweight/obesity/weight management • Prevalence of prediabetes, diabetes, and incident type 2 diabetes • HEDIS: Hypertension and Diabetes
ROSE [4]	• # of provider referrals for ROSE • # of patients w/ ROSE encounter (enrolled)	• Average # of ROSE sessions completed^a^ • Depression screening	Increase in telehealth care for mental health	• # of patients that return to VA post-partum (utilization of VA health services in the 12 months post-partum) • Mental health/depression

^a^This data will be collected as part of the EBP. All other data will come from CDW

We will include data on-site-, provider-, and patient-level variables from VA administrative data or our operations partners. For the sites, we will include facility type (VAMC or CBOC) and size, women panel size, proportion of women at site, type of comprehensive primary care model for women Veterans [4], number of designated women’s health providers, and urban/rurality. Provider characteristics will include provider type (MD or NP) and whether the provider is a designated women’s health provider. Patient-level controls will include sociodemographic characteristics, comorbidity including diabetes and cardiovascular risk, service-connected disability status, utilization, and the most common ICD-10 codes related to pregnancy status.

*Data analysis plan for Aim 2a*: We will use generalized linear models to evaluate the effectiveness of the intervention strategies for implementation of the EBPs in increasing women’s participation in telehealth-based preventive care. The models will account for clustering at the site level as well as incorporating site- and patient-level covariates outlined above. The main outcomes will include the composite measures of the proportion of women referred and enrolled in preventive telehealth care services, and the primary independent variable of interest is implementation using REP versus EBQI. We will conduct subgroup analyses by EBP to examine if the effects of the implementation strategies on proportion referred and enrolled vary by EBP (TLC or virtual DPP) as well as evaluate the effect on the *primary impact performance metrics* for telehealth care (weight management programs, Whole Health, and telemental health). In each model, we will examine the potential moderating effects of site-level characteristics (e.g., facility type, size, women’s health care program model, etc.). Adjustment for clustering will be performed using Stata v15, and we will evaluate goodness-of-fit using Mallows statistic (Cp). For DPP and TLC, we will use appropriate generalized linear models to assess weight and behavior change and examine differences by levels of participation (number of sessions completed). For ROSE, we will assess depression scores by levels of participation.

*Power calculations*: We based power calculations on the study’s basic single level of clustering sample design, where sites are randomized to receive either REP or EBQI to implement the EBPs. To detect a moderate effect size in terms of Cohen’s *D* (.26 standard deviations) between REP and EBQI, with 20 sites, and cluster adjustment (ICC=.01) with 80% power we will recruit 40 women per site (total of 800 women). We have considered all 20 sites to be separate clusters in terms of these calculations.

Aims 2b–2d are summarized in Table 3.

**Table 3 Tab3:** Overview of Aims 2b–2d

Method	Timing (per QUERI Roadmap)			Intended analyses
	Pre-implementation	Implementation	Sustainment	
Site tracking log	• Meeting minutes • Templated reflections • Stages of Implementation Completion (SIC)			2b: SIC 2c: Adaptations, experiences of EBP implementation 2d: cost
Semi-structured interviews	• CFIR-based pre-implementation interview	• CFIR-based post-implementation interview		2b: SIC 2c: Adaptations, experiences of EBP implementation
Periodic reflections	• Conducted approximately monthly to document: stakeholder engagement; EBP and/or implementation strategy adaptations; inner and outer setting influences; and planning, processes, and key events.			2b: SIC 2c: Adaptations, experiences of EBP implementation

*Aim 2b: Data sources*—The *Stages of Implementation Completion (SIC)* [27] is an assessment tool developed in a large randomized trial for the purpose of comparing “progress and milestones toward successful implementation…regardless of the implementation strategy utilized” [40]. SIC allows for quantitative scoring of sites’ implementation progress, reflecting multiple components of overall implementation success. The REP and EBQI teams will gather the information necessary to populate the assessment tool for each site.

*Aim 2b: Measures*—The SIC delineates a set of eight stages and activities across three phases (Pre-Implementation, Implementation, and Sustainment, consistent with the QUERI Roadmap [35]) that are largely universal in implementation efforts (e.g., readiness planning, adherence monitoring) [41]. The SIC may be unique among implementation measures for its utility in capturing standardized yet flexible assessments suitable for comparison across sites, EBPs, and implementation strategies.

*Aim 2b: Analysis*—SIC allows for calculation of the following scores: each site’s *stage score*, which describes the ultimate stage achieved at a given site; *proportion score*, which describes the proportion of activities completed by a site within a given stage; and *duration score*, which describes the amount of time a site spends in each stage. For additional detail on mixed-method analysis of SIC data, see *Aim 2c: Analysis*.

*Aim 2c: Data sources*—Adaptations of an EBP in practice [42], how individuals and teams engage in sensemaking around the EBP and implementation process [43], and stakeholders’ observations and experiences of implementation [28, 44] are all recognized for their importance in understanding implementation and sustainment outcomes [45]. We will evaluate adaptation, sensemaking, and experiences of implementation through interviews and brief structured data collection with *multilevel key stakeholders (KS)*, defined as individuals who are “responsible for…healthcare-related decisions that can be informed by research evidence” [46]. Consistent with the Women’s Health PACT cluster randomized trial of EBQI [29], eligible roles include regional leadership, facility leadership, facility-level clinical leaders such as WH Medical Directors, facility-level Women Veteran Program Managers, and PBRN Site Leads. Expanding beyond these roles for our prevention focus will allow the inclusion of primary care, primary care mental health integration (or mental health), and Whole Health/Health Promotion Disease Prevention leaders, program managers, and providers. Individuals in these roles will be identified using publicly available information as well as lists provided by the Site Leads. Using a snowball sampling approach, individuals in the eligible roles will be asked to recommend other KS due to their women’s health expertise. Based on our prior study, we estimate 6 KS per site (120 total) and 5 KS per VISN (20 total) for a total sample at pre-implementation of *n*=140. A similar sample size is anticipated for post-implementation/pre-sustainment KS interviews. Periodic reflections (see below) will be completed with *members of the implementation team* for each EBP and site (e.g., PIs, project managers, site leads, EBQI and REP leads, etc.).

*Aim 2c: Measures*—Adaptation, sensemaking, and experiences of EBP implementation will be assessed using KS interviews, structured data collection, and periodic reflections. Semi-structured qualitative interviews will be conducted with KS during pre-implementation and post-implementation/pre-sustainment phases. Pre-implementation interviews (see Additional file 2 for a draft interview guide) will examine usual care for the relevant care condition as well as CFIR domains including inner and outer setting, perceived characteristics of the intervention, characteristics of individuals (e.g., prior training), and implementation process using semi-structured interview guides informed by CFIR online resources and our work in EMPOWER QUERI 1.0 [22] and the Women’s Health PACT trial [25, 29]. Post-implementation/pre-sustainment interviews will also assess (1) CFIR domains (e.g., perceived characteristics of the EBP) and subdomains (e.g., relative advantages, complexity, etc.) and (2) recommendations for adaptations to and/or spread of the EBP to which KS were exposed.

We have developed a site tracking log that allows facilitators and other QI leads to document site contacts and meetings; the log format includes open-ended, templated written reflections on implementation progress from the external team member’s perspective. Logs will be used to document SIC progression and date of stage completion; capture information on dose and intensity of contacts across the two implementation strategies; support development of cost estimates per strategy, per EBP, and per site; and provide qualitative data from templated reflections for analysis as described below.

Periodic reflections [28] allow for consistent documentation of key activities and other implementation phenomena and have been shown to support timely and accurate documentation of adaptations, changes to inner and outer setting, team sensemaking, and dynamic experiences of EBP implementation. Periodic reflections will be conducted approximately monthly via telephone by a member of the Implementation Core with members of the implementation team for each EBP and site, will follow the template developed for use in EMPOWER 1.0 (Additional file 3), and will last 15–60 min, depending on the amount of current activity and number of team members participating in the call (range 1–4).

*Aim 2c: Analysis plan*—All *KS interviews* will be digitally recorded and securely transmitted to an approved transcriptionist for verbatim transcription. Transcripts will be reviewed, edited for accuracy, and summarized by the qualitative team. Consistent with our team’s approach across multiple projects, matrix analysis methods [47] will be used for rapid turn-around of the results to inform implementation processes. In-depth analysis of the qualitative data will be conducted using ATLAS.ti, a qualitative data analysis software program that allows for fluid interaction of data across types and sources. Initially, a top-level codebook will be developed for the pre-implementation interviews based on CFIR constructs and the semi-structured interview guide. This codebook will be elaborated upon based on emergent themes. Interviews will be compared within each site, across sites (e.g., to compare urban and rural sites), across implementation strategies, and over time. *Periodic reflections* and other sources of qualitative data (i.e., meeting minutes, templated reflections in site tracking logs, and archival information) will also be included in the data set and will be coded separately and in relation to the interview data, with particular attention to adaptations, individual and team sensemaking, and changes over time (e.g., within CFIR domains), similar to the processes previously used by members of this team [28]. Specifically, in the pre-implementation transcripts, we will identify commonly shared knowledge, attitudes, and beliefs related to the EBPs and their foci, and anticipated barriers to and facilitators of implementation. In post-implementation interview data, we will take a summative approach to characterizing overall experiences of and perspectives on implementation, with a particular focus on expectations for sustainment of the EBPs and the implementation strategies.

It is an innovation and strength of this proposal that we will combine 2b and 2c data sources to link qualitative (via interviews, reflections, etc.) assessments of CFIR constructs with implementation and effectiveness outcomes—including SIC scores for stage, duration, and proportion—for each EBP (virtual DPP, TLC, ROSE) and implementation strategy (REP, EBQI). With the exception of recent work by Palinkas et al., relatively few studies have previously investigated associations between CFIR domains and the stages and timing of implementation milestones achieved [40]. This will enable us to investigate, for example, whether EBQI, a strategy that requires more intensive activity in the initial stages and may thus be slower to reach implementation launch, is associated with improved sustainment, given that sites will be equipped with QI tools beyond the life of the project.

*Aim 2d: Data sources*—In line with current recommendations for budget impact analysis (BIA) for single payers [48] and within VA [49], we will compare costs associated with delivery of usual care with costs for implementation and delivery of our prevention-focused telehealth interventions (virtual DPP, TLC, ROSE) in terms of impact on short-term use of downstream health care resources. For example, we will evaluate whether the cost of implementing the ROSE intervention is associated with cost savings related to a reduction in need for specialty mental health care among women Veterans during the postpartum period.

*Aim 2d: Measures*—Core requirements for BIA include estimates of eligible population, current treatment mix and associated costs, expected treatment mix post-implementation and associated costs, and estimated changes in condition-related downstream costs [50]. Cost estimates for implementation strategies will be informed by site tracking log data (e.g., implementation dose in #hours/per site) as described in *Aim 2c: Data sources*. Healthcare utilization data will be drawn from CDW, as described for *Aim 2a: Data sources*, above.

*Aim 2d: Analysis*—Analyses will be structured to examine the comparative cost and outcomes of our two implementation strategies, REP and EBQI, as follows [30]: (Cost_Intervention_ + Cost_REP_) − (Cost_Intervention_ + Cost_EBQI_) vs. Outcome_InterventionW/REP_ − Outcome_InterventionW/EBQI_. Qualitative data collected for Aim 2c will also be examined to understand the “qualitative residual” that often remains underexplored in traditional quantitative economic evaluations, aiding in improved cost estimates and understanding of how stakeholders, staff, providers, and implementation teams make sense of implementation need, impact, and cost [30]. For example, cost estimates for an EBP may need to be updated based on adaptations in routine practice reported by providers in interviews. Similarly, leadership across sites may have differing perspectives on whether a higher-intensity strategy, like EBQI, is worth investing in given observed outcomes, with implications for future sustainment and spread efforts.

EMPOWER 2.0 will evaluate the business case for REP and EBQI in implementing DPP, TLC, and ROSE by first drawing upon the Cost of Implementing New Strategies (COINS) method for identifying resources invested in implementation [51]. COINS provides a systematic way of assessing costs associated with each Stage of Implementation Completion (SIC), which provides the blueprint for the business plan [27]. In establishing our cost estimates, we will integrate data from stakeholder interviews, site tracking logs, and reflections to assess costs as they occurred: (a) at each site, (b) for each EBP, (c) for both REP and EBQI, and (d) according to each stage of the implementation effort. As a measure of implementation process, the SIC will be cross-walked with the COINS to develop template plans and timelines for future adopters. Knowing, for instance, that they need to budget for 3 months of pre-launch preparation will allow new sites to plan against their fiscal years, e.g., knowing what to budget when, and what can be spread across different fiscal cycles.

